#### **Retention of trial participants.**

CFR retention protocols have yielded high retention rates with African American

families followed for time periods ranging from 3 to 14 years. At each data collection, family members provide contact information for three or more individuals who will always know their whereabouts. We gather email addresses, cell phone numbers, and Internet social networking addresses for participants and their primary contacts. Following each data collection visit, project staff contact participants to inquire about the quality of the experience, confirm contact information, and answer questions. Between data collections, we phone participants every 3 months to update contact information. Participants also receive a project newsletter that includes a stamped address correction form, as well as birthday cards and holiday cards. Experienced retention staff work with participants' contacts, CLs, and commercial databases such as NetDetective to locate lost participants. Participants' 5-year rates of mobility outside of Georgia are low (~3%). At each follow-up, we are prepared to send a data collection team to participants' homes throughout the region to collect data from families who have moved. For participants who leave the region, we collect data by phone or online; our research teams have experience with both modes of data collection.

## **Preventive Intervention Implementation Procedures**

Procedures for recruiting and training intervention facilitators, insuring curriculum fidelity, and engaging participants are based on our experiences in previous trials with rural African American families including the previous evaluation of SAAF and SAAF-T.

### **Intervention facilitators.**

SAAF/SAAF-T intervention facilitators are African Americans with a minimum education level of high school graduation. They are selected based on information from interviews and references that attest to their communication skills, engaging personalities, and ability to implement a structured program with fidelity. Facilitators will receive 30 hours of

training on the implementation of each program. Training includes curriculum activities, guided practice in delivering and pacing curriculum segments, and facilitator self-care. They will work from detailed manuals that describe all facets of program delivery. Didactic material, role-playing exercises, and modeling will be used to teach the protocol for each session. To ensure ongoing quality control and fidelity, facilitators will meet with the Prevention Coordinator weekly.

### **Intervention engagement and re-engagement.**

Families who are randomized to an intervention condition will receive an introductory visit from their assigned facilitator prior to the first group-based session. This visit is designed to familiarize parents with the program, answer questions about the intervention, and increase the family's comfort with the facilitator. During the visit, family members will view a promotional video describing the program. They will be asked about their weekly schedules, and sessions will be planned to accommodate the schedules of as many families as possible. To facilitate attendance, during the first half hour of each intervention session, a meal will be served to family members attending the session and any siblings of the target youth who accompany their parents. Assistance with transportation and on-site childcare will be provided on request. CLs will call all participants before the program begins and prior to each weekly session to encourage their involvement. Reminder postcards will be sent from the CFR each week, highlighting the focus of the upcoming meeting. A CL will call participants who miss a meeting to remind them of the next meeting and address any barriers to attendance. A \$25 honorarium will be provided to each family for each session attended, to defray any expenses associated with attendance. Feasibility of re-engagement. Engagement of the majority of families assigned to receive SAAF–Teen at mid-adolescence is made feasible by low rates of geographic mobility among rural African

American families in the targeted counties, and the routine retention and engagement protocols implemented by our experienced staff. Prior to implementation of SAAF–Teen in project year 4, families will have participated in ongoing data collection activities that involve a minimum of three home visits. At each home visit, families are reminded that they may be selected to participate in an intervention in the future. Data collection visits as well as the protocols discussed in Section C.4 (birthday cards, newsletters, etc.) strengthen families’ investment in the project. As with SAAF participants in project year 1, all families assigned to receive SAAF–Teen will experience the same protocols designed to achieve high rates of participation, including a program information visit, childcare and transportation assistance, a meal at each session, and a \$25 honorarium. Over 90% of eligible families of high school students agreed to participate in the SAAF–Teen program during the initial prevention trials .

#### **Prevention programs and program fidelity.**

Content and structure of the SAAF and SAAF–Teen programs are described in Section A. Complete facilitator manuals are provided in Appendix A (SAAF) and Appendix B (SAAF–Teen). Standardized procedures insure program fidelity. The intervention manuals include a detailed format to be used for each session. Each facilitator will be provided with materials designed to support correct execution of the session protocol, including an outline of each session, a checklist of the materials necessary for each activity, the specific theme of each task, and forms for in-session notes. Presentation of targeted processes on videotapes helps to ensure fidelity. Each session is audiotaped. Each team of facilitators is assigned an intervention supervisor, an expert trainer with a graduate degree in applied behavioral science, who will review session audiotapes with facilitators and provide weekly supervision of the intervention process. To assess program fidelity, session audiotapes will be scored for protocol adherence

using instruments validated in the SAAF and SAAF–Teen trials. Two judges will score 20% of the sessions to assess interrater reliability ( $\kappa$ ). In the past studies, mean coverage of the prevention curriculum components was >90%.

### **Data Collection Procedures**

At each of the five assessments, one 2-hour home visit will be made to each family for data collection. To minimize cultural bias, African American community members, many of whom have worked at CFR for years, will serve as field researchers. Field researchers will receive 16 hours of training and supervised practice that will address obtaining informed consent, building rapport, and helping participants to use the computer-based survey system. Field researchers will meet weekly with the Project Coordinator to discuss any problems that arise. Each year, a 5-hour refresher training course will be conducted. Data will be gathered via audio computer-assisted self-interviewing (ACASI) technology. Compared with face-to-face interviews and written surveys, ACASI elicits less social desirability bias and more accurate reports of socially sensitive issues. The user-friendly program guides respondents through the survey; those with low literacy skills are assisted through audio enhancements. ACASI was used successfully in prior trials. Consent/Assent. Parents will consent to their own and their youths' participation at each data collection visit. Youth will assent to participation. Consent/assent forms are provided in Appendix C.

### **Measures**

We selected measures validated with rural African American youth and parents in the SAAF and SAAF–Teen trials. Space limitations preclude full descriptions of the measures indexing SAAF and SAAF–Teen targeted protective processes; see Appendix D for copies of all measures.

**Demographics (Waves 1-5).**

Primary caregivers will report their yearly income, per capita income, employment status, duration of unemployment during the past 2 years, hours worked per week, education level, numbers of children and adults in the household, and relations of all household members to one another.

**Alcohol and other drug use (Waves 1-5).**

The substance use assessment is designed to address the multidimensional nature of use. Items were selected from three well-validated measures for their sensitivity to intervention effects in our previous research at several levels of substance use. At the initiation level, group differences in the proportion of participants who transition from nonuse to use during the study can be detected. At the escalation level, group differences in the proportion of participants who increase their frequency/intensity of use during the study can be assessed. At the problem use level, group differences in specific substance-related behaviors and problems can be indexed. The basic items in the measure are those included in the Monitoring the Future study, which assess lifetime, annual, and 30-day prevalence and frequency of cigarette smoking, alcohol use, binge drinking, and marijuana use. For the purposes of the proposed study, a 3-month assessment will be added. A checklist of other drugs includes lifetime use of LSD/acid, Ecstasy, cocaine, heroin, other opiates, amphetamines, non-prescribed tranquilizers, and inhalants. Problems associated with substance use will be indexed using items from the Minnesota Student Survey for high school students and the Rutgers Alcohol Problems Index. These scales include items assessing dependence (e.g., had to use more to get same effect, tried to cut down but couldn't) and negative consequences of use (e.g., hurt relationships with friends or family, interfered with other activities, resulted in legal problems, missed school or work).

**SAAF Targeted Protective Practices (Waves 1-3).**

The SAAF Intervention-Targeted Processes instrument assesses parenting and individual youth processes on which SAAF sessions focus. The battery includes parallel versions of items that permit youth and parents to report the frequency of parenting practices and parent-youth relationship dynamics we termed *regulated/communicative parenting*. Items include those from well-established measures of relationships climate, disciplinary practices, and racial socialization processes that were adapted for African American families with the assistance of focus groups, as well as items specifically written for the SAAF trial and validated with those data. Subscales, confirmed via factor analysis, include involved vigilant parenting, racial socialization, and clear expectations about alcohol use and other risky behavior. Items assess behavior in the past 6 weeks with responses that range from 1 (*never*) to 5 (*always*). Cronbach's alphas for the subscales ranged from .70-.92 in our prior prevention research and were sensitive to intervention participation. Items assessing youths' *intrapersonal protective processes* targeted in SAAF include the following subscales: *behavioral and emotional self-regulation, racial identity, prototypes of alcohol-using peers, and resistance efficacy*. Youth report their intrapersonal protective processes and parents report their observations of youths' self-control. As with the family items, these scales were developed from existing items, adaptations derived from focus group feedback, and specific items written for the SAAF trial. They were confirmed with factor analyses, and Cronbach's alphas ranged from .68-.90.

**SAAF-Teen Targeted Protective Practices (Waves 4 and 5).**

The SAAF-Teen Intervention-Targeted Protective Processes instrument (see Appendix D for all items) assesses parenting and individual youth processes on which SAAF-Teen sessions focus. As with the SAAF instruments, the SAAF-Teen battery includes parallel versions

of items that permit youth and parents to report the frequency of developmentally appropriate parenting behaviors that we termed *competence-promoting parenting*. Many items represent developmentally appropriate items, adapted via wording changes and behavioral emphases, of items used in SAAF (limit setting, consistent discipline) as well as new items that address unique intervention targets such as parents' provision of support and coaching for dealing with discrimination and for planning academic and vocational careers. Additional items address parental involvement in youths' educational pursuits and problem-solving interactions that foster youths' sense of autonomy and competence. Youth subscales emphasize goal setting and planning; self-regulatory processes and skills for coping with stress, particularly racial discrimination; and decision-making processes in peer contexts. Subscale reliability ranged from .70-.92 in our prior prevention research, and the scales were sensitive to intervention participation .

## **Data Analysis**

### **Data management, exploratory data analysis, psychometrics, and experimental considerations.**

Data will be organized and cleaned following quality control procedures that involve analyses of outliers and unexpected or inappropriate missing-data patterns. Next, items' distributions and constructs' psychometric properties will be examined. We will establish equivalence among experimental conditions with ANOVAs and chi-square tests on baseline levels of alcohol use, preadolescent protective processes, and demographic variables. Any departures from equivalence will be controlled in subsequent analyses. All primary analyses will be intent-to-treat.

### **Differential retention and intervention participation.**

Our prior experience and the aforementioned retention and intervention engagement procedures support our expectation that attrition will pose minimal threats to the internal validity of the study. We will, however, investigate the possibility of differential retention or participation by experimental condition. When data are missing consistent with a “missing at random” (MAR) assumption, we will test hypotheses with models that handle missing data using full maximum likelihood (FIML) methods in which all available data are included. Non-ignorable missing data will be managed with procedures that explicitly model “missingness mechanisms” to develop unbiased causal parameters. For example, although unlikely, if experimental groups report differential attrition or levels of participation in assigned interventions, complier average causal effect (CACE) methods can be used to estimate accurately the causal effect of dual inoculation versus other groups. CACE models use a mixture modeling framework to develop groups based on compliance status. Comparisons of treatment groups among the “compliers” provide unbiased estimates of causal effects.

#### **Aim 1.**

Mean differences in alcohol use by experimental group at wave 5 (~10 months after SAAF-T implementation) will be tested with structural equation models (SEM) as presented in Figure 6. These models are roughly equivalent to ANCOVA, but the SEM software permits FIML-based estimation of parameters as well as options for forming latent alcohol use constructs and greater precision in specifying and testing model parameters. We will investigate main effects on onset, frequency of use, binge use, and alcohol use problems as well as aggregate alcohol risk indices validated in prior trials to establish mean differences in use as a

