# Trial Protocol

## Participants

A random sample of 460 African American youth in 5th grade and their primary caregivers will be recruited for the proposed study. Families will be sampled from 8 Georgia counties. We selected nonmetropolitan counties (population density <100 persons per square mile) with large proportions of African American residents (>25%) that represent the range of non-urban environments in the South in which African American live . These areas are demographically and economically similar to those in which SAAF and SAAF–T were originally tested. Table 1 presents county demographic characteristics. In past trials, we examined the possibility that county heterogeneity in these indicators affected intervention response: no effects were detected 

| Table 1. Demographic characteristics of the counties to be included in the sample (AA = African American) |        |               |                               |            |
|-----------------------------------------------------------------------------------------------------------|--------|---------------|-------------------------------|------------|
| County                                                                                                    | AA (%) | Single Parent | Median AA Family Income (\$k) | AA <HS (%) |
| Baldwin                                                                                                   | 43     | 48            | 26.2                          | 38         |
| Burke                                                                                                     | 50     | 51            | 17                            | 45         |
| Emanuel                                                                                                   | 32     | 50            | 15.6                          | 47         |
| Green                                                                                                     | 38     | 50            | 21.4                          | 46         |
| Laurens                                                                                                   | 35     | 49            | 20.0                          | 43         |
| MacDuffie                                                                                                 | 38     | 50            | 20.1                          | 50         |

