### Random assignment and contamination.

After pretest, families will be assigned randomly to one of four experimental groups: (a) *preadolescent inoculation*, (b) *mid-adolescent inoculation*, (c) *dual inoculation* control, and (d) control. Although the efficacy of SAAF and SAAF–Teen have been established, inclusion of a

control condition provides a baseline from which to compare normative alcohol use behavior in the population to both single- and dual-inoculation groups; it is also essential for comparing the single inoculations' economic efficiency. Preadolescent inoculation families will be assigned to receive SAAF at age 11 with no further intervention. Mid-adolescent inoculation families will receive SAAF–Teen at age 14. The dual-inoculation group will be assigned to receive both SAAF at age 11 and SAAF–Teen at age 14. The control condition involves no intervention contact. Participants will be notified if they are selected to participate in SAAF shortly after pretest. No participants will know if they are to receive SAAF–Teen until several months prior to its implementation. For each intervention implementation, families who are not attending a program receive written information by mail regarding adolescent development and alcohol use. Sending these materials is intended to maintain investment in the project for families who are not attending an intervention. No alcohol use effects are expected based on receiving written materials. All families will be followed across the course of the proposed study and assessed regardless of the number of intervention sessions they attend (intent-to-treat design). Information will be collected from family members about their participation in family enrichment programs offered in the school or community. The potential effects of participation in other programs (contamination) will be examined and statistically controlled in data analyses, as Lang et al. described.

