### Power.

For experimental comparisons among four groups, a sample size of 100-115 families per group is sufficient to detect an effect of .13 with .80 power ( $\alpha < .05$ ) and a power of .90 for an effect as small as .15. For growth curve analyses ( $n > 100$  per group), we used algorithms to estimate the smallest intervention effect size we can detect with 80% power for changes in the slope parameter, assuming linear growth over four time points. With measurement reliability of 60%, we can achieve 80% power when the ES is 0.1 at posttest and ES is 0.2 at long-term follow-up. This suggests that we will have sufficient power to detect small to moderate intervention effects over time.

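### The four arms form a complete 2x2 of SAAF by SAAF-Teen, but the readable Aim 1 text names no contrasts and plans no interaction estimate, and the stated power fits only a one-degree-of-freedom contrast on all 460 families

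*Combined protocol and SAP*

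**What the plan says.** Under Random assignment and contamination, "families will be assigned randomly to one of four experimental groups". Their content is:

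- SAAF only: "Preadolescent inoculation families will be assigned to receive SAAF at age 11 with no further intervention".
- SAAF-Teen only: "Mid-adolescent inoculation families will receive" SAAF-Teen at age 14.
- Both: "The dual-inoculation group will be assigned to receive both SAAF at age 11" and SAAF-Teen at age 14.
- Neither: "The control condition involves no intervention contact".

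Aim 1 tests "Mean differences in alcohol use by experimental group at wave 5", about 10 months after SAAF-Teen, with structural equation models described as close to ANCOVA and presented in Figure 6, which is not shown. It speaks of main effects on a list of alcohol outcomes. It names no SAAF factor, SAAF-Teen factor, product term, contrast set or order of tests. Outcomes may be modelled as logistic, continuous, Poisson or negative binomial.

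The Power section begins "For experimental comparisons among four groups". It states that 100-115 families per group give .80 power for an effect of .13 and .90 for .15. The effect metric is not stated.

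Dual inoculation is set against the other arms in two further places. Aim 3 makes it the cost-effectiveness hypothesis, names the three comparators and takes outcome effects from the Aim 1 analyses. The section on differential retention mentions it for a complier analysis, to be used if attrition or participation differs by group.

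**The concern.** Two crossed randomised programmes allow three kinds of question: is dual better than a single programme, what does each programme do on average, and does one programme change the effect of the other? The readable Aim 1 text does not say which of these will be tested, and the third has no planned estimate anywhere in it.

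Two things are at stake. First, without named contrasts, a report can drift into comparing which arms reach significance against control. If dual differs from control and neither single arm does, that invites the conclusion that both programmes are needed together. Simple additivity produces the same pattern often. Second, the power statement does not say which comparison it covers, and the answer differs widely between a factor effect, a two-arm contrast and a four-group test.

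**Working it through.** **Inputs.** "A random sample of 460 African American youth" (Participants); 13% attrition, leaving 400 completers (Repeated assessments and attrition); effects .13 and .15 with power .80 and .90 (Power). Assumed: equal allocation (115 randomised and 100 completing per arm), two-sided alpha .05, SD 1, no gain from covariates, and effects read as Cohen's f.

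**1. The plan's own figure.** Power from the noncentral F with λ = N·f². For N = 460, λ = 460 × .0169 = 7.77 at f = .13, and 460 × .0225 = 10.35 at f = .15.

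| Test | Families | Power at .13 | Power at .15 |
|---|---|---|---|
| 1 df, all arms | 460 | .795 | .894 |
| 1 df, all arms | 400 | .737 | .849 |
| 3 df, four groups | 460 | .636 | .773 |
| 3 df, four groups | 400 | .568 | .707 |
| Two arms | 230 | .501 | .620 |
| Two arms | 200 | .448 | .560 |

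Only the first row reproduces .80 and .90. The 3-df test would need about 649 and 634 families, or covariates explaining 28-29% of variance at N = 460 (37-39% at N = 400). The 1-df test at N = 400 would need 14-15%. The documents give no such figure.

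Other readings of the metric: a correlation gives .798 and .898 on 460 families, again a full-sample 1-df test. A standardised mean difference gives .286 and .363 even for two arms against two at 115 per arm. Read as f², power is essentially 1.

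**2. Precision by contrast**, n families per arm. The detectable difference at 80% power is (1.96 + .84) × SE.

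- Two arms, such as dual - preadolescent: SE = √(2/n) = .141 at n = 100 (.132 at 115); detectable .40 SD (.37).
- Factor effect, such as [(dual + mid) - (preadolescent + control)]/2 for SAAF-Teen: SE = √(1/n) = .100 (.093); detectable .28 SD (.26).
- Interaction, (dual - mid) - (preadolescent - control): SE = √(4/n) = .200 (.187); detectable .56 SD (.52).

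The factor effect uses 400 completers and the two-arm contrast 200, so its variance is half. For two equal halves d = 2f, so f = .13 is d = .26. At d = .26, power is .74-.80 for a factor effect, .45-.51 for a two-arm contrast and .25-.29 for an interaction of that size.

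**3. How often additivity misleads.** 400,000 simulated trials per setting, normal outcome, each programme lowering use by d, effects adding exactly.

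- Dual differs from control and neither single arm does: 40% of trials at d = .20; 35% (n = 100) and 31% (n = 115) at d = .26.
- Dual beats both single arms at d = .26: 29% and 34%.
- Both factor effects significant at d = .26: 55% and 63%. The two are independent, so .739² = .55 and .796² = .63.
- Interaction falsely significant: 5%.

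**4. How a factor effect can mislead.** Let both single arms and dual all lie .26 SD below control, so SAAF-Teen adds nothing after SAAF. The SAAF-Teen factor effect is then (.26 + 0)/2 = .13 SD, significant in 25% (n = 100) to 29% (n = 115) of trials. The interaction is missed in 71-75%. In 19-20% the factor effect is significant and the interaction is not. Dual versus preadolescent keeps its 5% error.

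**The case against.** The strongest reply is that the useful comparison is already there. A reader might infer that no test asks whether the second programme adds. The documents do not support that: dual against preadolescent asks exactly this, it is one of the Wave 5 group differences, and Aim 3 names dual against each other arm. What is missing is its pre-specification in Aim 1, and any estimate of interaction.

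A reader might also infer that Aim 1 treats the arms as four unordered groups, so that every programme effect uses half the families. That is not established. The coding is unstated and Figure 6 is not shown. The reference to main effects is attached to outcomes rather than to factors, but it does not exclude factor coding, and the power figures fit a full-sample contrast. The loss of precision therefore applies to two-arm contrasts, not to a plan that can be read.

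Three further objections stand and shape the remedy. Factor effects average over the other programme and mislead under redundancy (step 4). Interaction depends on scale: effects that add on a logit or log scale do not add in means, and Aim 1 allows several outcome models. Finally, nothing in the documents proposes inferring synergy from separate tests against control; that is a risk left open, not a stated intention. The section setting out the programmes' background is not in the document, so interaction cannot be called the trial's central question.

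**Conclusion.** The point holds as a gap in specification. The design is a complete 2x2, and the readable Aim 1 text states neither its coding nor its contrasts and plans no interaction estimate. The choice of contrast changes the detectable difference from .28 to .40 SD at 100 completers per arm. The stated power of .80 and .90 belongs to a 1-df contrast on all 460 randomised families if the effects are Cohen's f. On the same reading, no comparison examined reaches those values at 400 completers without covariate gain. With purely additive effects of .20-.26 SD, 31-40% of trials would show a pattern that suggests both programmes are needed.

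The sizes rest on equal allocation, two-sided .05, a normal outcome in SD units and no covariate adjustment. Adjustment would shrink all three standard errors together and leave their ratios unchanged. The .26 SD is not in the documents; it is 2 × .13 under the Cohen's f reading.

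**What to change.** In the Aim 1 text:

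1. State the coding of the arms, and name dual versus preadolescent and dual versus mid-adolescent as the contrasts that answer whether dual is better.
2. Add (dual - mid) - (preadolescent - control) as an estimate with a 95% CI, with the scale stated for each outcome model.
3. Report the two full-sample factor effects, labelled as averages over the other programme and not as evidence that the second programme adds.
4. State that no claim of synergy, redundancy or need for both programmes will rest on which arms separately differ from control.
5. Restate power for each contrast at 400 completers, naming the effect metric and any assumed covariate R².

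The cost is SAP wording, with the same data, model and software. The downside is that the interaction will be imprecise: its 95% CI half-width is about 1.96 × .20 = .39 SD at 100 per arm. It should be presented as descriptive and cannot serve as a gate for the factor effects.

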### **Repeated assessments and attrition.**

Families will participate in 5 annual assessments. Wave 1, the baseline assessment will occur when youth are age 11 and approximately 3 months prior to implementation of SAAF. Wave 4 will occur just prior to the implementation of the SAAF–Teen. The final assessment, Wave 5, occurs approximately 10 months after implementation of SAAF—Teen. In previous

basic research and prevention trials

conducted at CFR, 5-year retention

rates ranged from 88% to 92% .

We plan conservatively for a 13%

attrition rate, ensuring that 400

[figure not shown]

participants (87% of 460) will complete the trial. Figure 5 presents the project timeline.

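### Aim 1 tests at least five co-equal alcohol outcomes across four arms with no primary outcome, contrast order or multiplicity control in the supplied text

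*Combined protocol and SAP*

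**What the plan says.** Under Random assignment and contamination, "families will be assigned randomly to one of four experimental groups": preadolescent (SAAF), mid-adolescent (SAAF–Teen), dual, and control.

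Under Aim 1, Wave 5 group differences "will be tested with structural equation models (SEM) as presented in Figure 6". The outcomes are given in one list: "We will investigate main effects on onset, frequency of use, binge use, and alcohol use problems as well as aggregate alcohol risk indices". Indices is plural, so there are at least five. Outcome distributions are to be chosen as appropriate, and growth-curve comparisons are to be considered as well. Only marijuana and nicotine are called ancillary, so no alcohol outcome ranks below another.

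The alcohol items in the Measures section cover "lifetime, annual, and 30-day prevalence and frequency of cigarette smoking, alcohol use, binge drinking, and marijuana use", and a 3-month window is added for this study. Aim 1 does not say which window feeds which outcome. On timing: "The final assessment, Wave 5, occurs approximately 10 months after implementation of" SAAF–Teen.

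The Power section says the trial can "detect an effect of .13 with .80 power ( $\alpha < .05$ ) and a power of .90 for an effect as small as .15" with 100–115 families per group. That is the only alpha stated for Aim 1. The opening Data Analysis paragraph calls the primary analyses intent-to-treat but names no primary outcome. Aim 1 lists no contrasts. Aim 3 sets dual inoculation against each of the other three arms.

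**The concern.** Four arms and several equal outcomes allow many routes to a positive finding, and the text does not say in advance which result answers the main question. If any favourable contrast on any alcohol outcome may be reported as evidence for dual inoculation, the error rate of that claim is well above the level of a single test.

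The consequences go beyond Aim 1. The Aim 2 section uses Aim 1 as the baseline for mediation, and the Aim 3 section takes its outcome effects from the Aim 1 analyses. A chance finding selected in Aim 1 would carry into both.

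**Working it through.** **Inputs from the documents:** four arms; 100–115 families per arm (400–460 in total); alpha .05; at least five Aim 1 alcohol outcomes; Wave 5 about 10 months after SAAF–Teen; programme length 5 or 7 weeks (Aim 3).

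**Assumptions:** equal allocation; two-sided tests; three dual contrasts (dual versus control, preadolescent, mid-adolescent), as in Aim 3; between-outcome correlation ρ, which is not given and is taken from 0 to .9.

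**1. The plan's own power figure.** Read the effect as Cohen's f, with noncentrality λ = N·f². For N = 460, λ = 460 × .13² = 7.77 and 460 × .15² = 10.35.

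- One 1-df test, N = 460: power .795 and .894. This reproduces .80 and .90.
- One 1-df test, N = 400: .737 and .849.
- 3-df omnibus test, N = 460: .636 and .773; N = 400: .568 and .707.
- 3-df test with covariates, λ = N·f²/(1 − R²): .804 and .910 at N = 460 with R² = .3; .810 and .914 at N = 400 with R² = .4. The documents state no R².

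The figure therefore fits a single test at .05. With Bonferroni, the 1-df power for f = .13 at N = 460 falls from .80 to .65 (3 tests), .58 (5 tests) or .44 (15 tests).

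**2. False-positive rate.** Five outcomes × three contrasts = 15 tests. If they were independent, 1 − .95^15 = .537. They are not: the contrasts share the dual arm, and the outcomes are correlated. I simulated standardised arm means with all arms equal, x(g,k) = √ρ·u(g) + √(1 − ρ)·e(g,k), where u and e are standard normal. The test statistic is z = [x(dual,k) − x(g,k)]/√2, significant if |z| > 1.96, with positive z taken as favouring dual. There were 600,000 replicates per setting.

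| Rule (five outcomes) | ρ = 0 | .3 | .5 | .7 | .9 |
|---|---|---|---|---|---|
| At least one of 15 dual contrasts favours dual | .277 | .240 | .209 | .171 | .120 |
| At least one of 15, either direction | .489 | .458 | .409 | .340 | .240 |
| One omnibus test per outcome | .226 | .212 | .188 | .154 | .105 |
| Dual vs control only, either direction | .225 | .209 | .183 | .148 | .101 |
| Dual contrasts only after a significant omnibus, either direction | .184 | .174 | .156 | .129 | .088 |
| Dual beats both single arms on the same outcome | .023 | .022 | .020 | .017 | .011 |

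A single two-sided .05 test falsely favours dual with probability .025. So .171 to .240 is about 7 to 10 times that (.171/.025 = 6.8; .240/.025 = 9.6).

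**3. Recall windows at Wave 5.** Counted from the start of SAAF–Teen, a 12-month item reaches back 12 − 10 = 2 months before it, or 2/12 = 17% of the window. Counted from its end, subtract the programme length: 5 weeks is 1.15 months and 7 weeks is 1.61 months, leaving 0.85 or 0.39 months (7% or 3%). The 3-month and 30-day windows lie wholly after SAAF–Teen.

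**4. Power for a joint claim.** For one pairwise contrast at .80 power, unadjusted and on a continuous scale, d = (1.96 + 0.842)·√(2/n) = .396 at n = 100 and .369 at n = 115. Two contrasts sharing the dual arm correlate .5, so at that effect both succeed with probability about .69.

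**The case against.** The strongest reply is that the error rate depends on a decision rule the plan does not contain. Nowhere does it say that one significant result establishes the benefit of dual inoculation. Aim 1 likens the models to ANCOVA and allows latent alcohol constructs, which could combine outcomes. If dual must beat both single arms on the same outcome, the rate with all arms equal is about 2%. This stands, and it is why the size has to be given by rule. It does not remove the concern, because the supplied text commits to none of these rules. Nor does the 2% hold generally: if dual truly and clearly beats one single arm but equals the other, the joint rule reduces to one contrast on five outcomes. The chance of a favourable result is then about half the dual-versus-control row, 7–10% at ρ of .7 to .3.

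Two limits also stand. Testing each contrast at .05 is inferred from the power paragraph. Figure 6 and Section A are not in the supplied text, so a hierarchy stated there cannot be excluded.

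A reader might infer three stronger points:

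- **That 34–46% is the chance of falsely claiming a benefit.** It counts results in which dual looks worse; the favourable half is 17–24%.
- **That the annual and lifetime windows add false positives.** They do not. They can only dilute a SAAF–Teen effect, mainly in mid-adolescent versus control and dual versus preadolescent, and Aim 1 does not say these windows are used.
- **That lifetime onset is therefore invalid.** In arms given SAAF at age 11, use before Wave 4 is legitimate post-randomisation outcome time.

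**Conclusion.** The concern holds. In the supplied text, Aim 1 has at least five co-equal alcohol outcomes, four arms, and no primary outcome, contrast order or multiplicity control. With 15 two-sided tests at .05 and outcome correlation .3–.7, the chance of at least one false result favouring dual inoculation is about 17–24%. One omnibus test per outcome, or dual versus control alone, gives about 15–21% in either direction.

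The correlation and the 15-test rule are assumptions, so the range should be quoted with them. Repeated recall windows, additional indices and growth curves are not counted and would add opportunities. The recall windows matter here only for choosing the primary outcome. The documents do not support calling the power figure wrong: it can be reproduced, but as a single test with no allowance for multiplicity.

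**What to change.** Before Wave 5 outcomes are analysed by arm, state in the Aim 1 section:

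1. One primary Wave 5 alcohol outcome, with its recall window. Frequency over the added 3-month window is one candidate, because it lies wholly after SAAF–Teen. The documents give no prevalence or sensitivity for it, so the sponsor should check that before choosing.
2. A fixed sequence at two-sided .05: dual versus control; then, only if that is significant, dual versus preadolescent and dual versus mid-adolescent. Both must be significant in favour of dual for a claim that dual is better than single.
3. All other alcohol outcomes, windows and growth models as secondary, with Holm or false-discovery-rate control.
4. Lifetime onset kept as a valid outcome for contrasts that include SAAF. New onset after Wave 4 is at most a supplementary analysis of the SAAF–Teen effect.

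If Figure 6 or Section A already sets a hierarchy, restate it here.

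The cost is SAP wording; no new data are needed. The other outcomes lose confirmatory status. The joint requirement has less power than one contrast (about .69 where each contrast alone has .80), and the Power section should say so and give power for these contrasts.
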